### Outcome measures

The primary outcome of the RaDIANT Community Study is the change in facility-level transplant referral (for patients <70 years) from baseline. Baseline referral will be calculated as the average number of unique referrals in a dialysis facility over the 12-month period preceding the intervention (January-December 2013) divided by the total number of ESRD patients within the facility for that time period. Post-intervention crude referral will be measured as the average number of unique referrals generated from January-December 2014 divided by the total number of ESRD patients within the facility for the same 12 month intervention period. As described above, referral will be defined as the receipt of a referral by the transplant center. Patient-level transplant referral data with facility identifiers will be collected from all of the transplant centers in GA and aggregated to summarize the total number of referrals to any transplant center in the state divided by the total number of adult ESRD patients <70 years in the facility. If facility characteristics are not equally distributed at baseline between control and intervention groups, we will consider adjustment using a Standardized Transplantation Referral Ratio (STRR). The STRR will be defined as the total number of observed transplant referrals within a facility divided by the total number of expected referrals based on the state average and adjusting for relevant covariates, among patients aged 18–69 [similar to the Standardized Transplantation Ratio (STR) used by CMS] [1].

A secondary outcome of interest is the reduction in AA vs. white racial disparity in transplant referral. The reduction in racial disparity will be measured as the difference in the proportion of referrals among AA vs. whites. Furthermore, we will examine whether the total number of AA ESRD patients referred for transplant in the state of GA increased from baseline to 12 months to examine the absolute impact of the RaDIANT Community Study on improving access for AA ESRD patients in the state.

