### Statistical analyses

Descriptive analyses of facility-level baseline variables (demographic, clinical characteristics and transplant access measures) will be compared and differences between study arms at baseline will be evaluated using either *t* tests or their non-parametric equivalents for continuous variables and chi-square test for categorical variables. Significant differences in baseline characteristics will be adjusted when assessing the overall intervention effect as described above.

To evaluate the effect of the intervention on improvement in transplant referral by study arm, we will calculate the difference in facility-level transplant referral rate from baseline to 12 months for each facility in the study. Analysis of covariance (ANCOVA) will be used to test for post-intervention mean differences in referral rates for the control and intervention group after adjusting for the baseline referral rates and facility characteristics that differed significantly across the two arms at baseline. For skewed outcomes, differences in the intervention and control groups will be evaluated using a non-parametric Wilcoxon rank sum test.

For our secondary outcome, AA vs. white racial disparity in transplant referral, we will examine whether (i) the proportion of AA patients referred for transplantation increased from baseline to 12 month follow up at the facility level and (ii) whether there is a differential effect in the intervention group compared to the control group over time, after adjusting for between facility heterogeneity. A mixed effects model will be used to test for differences in the proportion of AA patients referred between baseline and 12-month follow up in the two study arms respectively. Fixed main effects of (a): time (measured in months from baseline; baseline assumed month 0) (b): intervention status (control = 0, intervention = 1), and (c) their interaction on referral disparity, averaged across different subpopulation of facilities will be assessed. Facility level random effects (intercepts and slopes) will be considered to adjust for variations in the average time trend due to unmeasured confounding independent of the intervention. If the individual facility trajectories indicate a similar time trend (slope), a random intercept only model will be sufficient to account for between facility heterogeneity at baseline.

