### Power and sample size calculations

Our sample size calculations are based upon our primary aim to improve access to kidney transplant referral and also feasibility and resource availability for intervention activities. To test the primary null hypothesis of no difference in referral proportions between the control and intervention groups, our sample size of 134 dialysis facilities (67 facilities in each arm), with an estimated 46 patients per facility, achieves 80% power to detect a moderate difference of 3.1% to 4.8% in referral proportions between the two groups at 5% significance level. The power calculation assumes a 14% crude referral proportion in the control group based on baseline referral data and an intra-cluster correlation coefficient (ICC) of 0.01 to 0.05, respectively, to account for between-facility variation.

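### With one 2013 and one 2014 value per facility, the slope-selection rule for the African American referral model cannot be applied, and its random-intercept fallback is a valid but inefficient change-score comparison; a common-baseline model is a free improvement

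*Protocol article*

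**What the plan says.** The Statistical analyses section sets two questions for the disparity outcome: (i) whether the proportion of African American patients referred rose from baseline to 12 months, and (ii) whether the change differs between arms. A mixed model contrasts baseline with 12 months. Its fixed effects are time in months (baseline is month 0), arm, and time by arm.

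The random effects are left open: "Facility level random effects (intercepts and slopes) will be considered". The choice between the two structures is made on the observed data: "If the individual facility trajectories indicate a similar time trend (slope), a random intercept only model will be sufficient".

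For the primary outcome, the same section uses ANCOVA on the follow-up rate adjusted for the baseline rate.

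The Outcome measures section defines facility referral as one aggregate for calendar year 2013 and one for 2014, the latter as the "average number of unique referrals generated from January-December 2014 divided by the total number of ESRD patients". That definition is written for the primary outcome; none is given separately for the mixed model.

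**The concern.** Two annual proportions per facility are enough to estimate a mean change. They are not enough to tell a facility's own slope from residual noise when the residual variance is a free parameter. A rule that inspects trajectories before deciding whether to keep slopes then has no usable input.

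The model left over includes an arm effect at month 0, so it lets the arms differ at baseline although they were randomised. It thereby discards the information that makes ANCOVA more precise for the primary outcome. At stake is precision on the trial's secondary aim, reduction of racial disparity in referral. The validity of the facility-level comparison is not in question.

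**Working it through.** **Inputs.** From Power and sample size calculations: "our sample size of 134 dialysis facilities (67 facilities in each arm), with an estimated 46 patients per facility"; 14% referred among controls; ICC between 0.01 and 0.05. From Table 1: 65.4% of patients in the randomised pool are African American, so m = 46 × 0.654 ≈ 30 per facility. The between-year correlation of facility values is not given and is assumed below.

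**1. The plan's own figure.** The article states "80% power to detect a moderate difference of 3.1% to 4.8% in referral proportions between the two groups at 5% significance level" for the primary outcome. Effective n per arm = 67 × 46 / (1 + 45 × ICC).
- ICC 0.01: 3082/1.45 = 2125.5; power at 3.1 points is 79.7%, detectable difference 3.11 points.
- ICC 0.05: 3082/3.25 = 948.3; power at 4.8 points is 80.6%, detectable difference 4.76 points.

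Both reproduce with a two-sided test. No power figure is stated for the disparity model.

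**2. Identifiability.** Let the random intercept variance be a, the intercept-slope covariance b, the slope variance c and the residual variance e. At months 0 and 12:
- Var(Y0) = a + e
- Cov(Y0, Y12) = a + 12b
- Var(Y12) = a + 24b + 144c + e

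There are three equations for four unknowns (rank 3), so c cannot be separated from e. With a monthly series the rank is 4.

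**3. Inspecting trajectories.** Two points always lie on a line. Binomial noise in one facility's change has SD √(2 × 0.14 × 0.86/30) = 9.0 points. At ICC 0.05, with an assumed between-year correlation k of facility effects of 0.9 to 0.7, the true SD of change is √(2 × 0.05 × 0.1204 × (1 − k)) = 3.5 to 6.0 points. The plotted slopes show mostly noise.

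**4. What the fallback is.** The random-intercept model was fitted to two simulated data sets and compared with change scores and ANCOVA:

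| ICC | Mixed model, interaction × 12 (SE) | Change score (SE) | ANCOVA SE |
|---|---|---|---|
| 0.01 | 0.07264 (0.01562) | 0.07264 (0.01562) | 0.01217 |
| 0.05 | 0.04925 (0.01639) | 0.04925 (0.01639) | 0.01532 |

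The first two analyses are the same.

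**5. Efficiency.** With equal variances and correlation rho, the change-score variance is proportional to 2(1 − rho) and the baseline-adjusted variance to 1 − rho². The ratio is 2/(1 + rho). Take rho = r·m·ICC/(1 + (m − 1)·ICC), where r is the persistence of the facility effect (assumed 0.5 to 1). The last column is change-score power where ANCOVA has 80%.

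| m | ICC | r | rho | Variance ratio | Power |
|---|---|---|---|---|---|
| 30 | 0.01 | 1.0 | 0.233 | 1.62 | 60% |
| 30 | 0.01 | 0.5 | 0.116 | 1.79 | 55% |
| 30 | 0.05 | 1.0 | 0.612 | 1.24 | 71% |
| 30 | 0.05 | 0.5 | 0.306 | 1.53 | 62% |
| 46 | 0.05 | 1.0 | 0.708 | 1.17 | 74% |

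In 2000 simulated trials per setting (30 patients per facility, r = 1), power for change score against ANCOVA was 50% v 69% (ICC 0.01, 3.1 points) and 86% v 92% (ICC 0.05, 4.8 points).

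**6. If patient-level records are used.** Dropping facility-by-year variation when it exists understates the variance of the arm contrast by [ICC(1 − k) + (1 − ICC)/30] / [(1 − ICC)/30]. At ICC 0.05 the base term is 0.95/30 = 0.0317.
- k = 0.9: 0.0367/0.0317 = 1.16, type I error 6.9%.
- k = 0.7: 0.0467/0.0317 = 1.47, type I error 10.6%.

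**The case against.** **Two occasions is an inference.** Time is counted in months, the text speaks of trajectories, and the transplant centers supply dated referrals, so a monthly series is possible. Slopes would then be estimable and the change-score equivalence would not follow. This stands, and the point is conditional on it. Two annual values remains the more natural reading: the contrast is baseline against 12 months, no monthly outcome is defined, and the monthly facility reports come from intervention facilities only.

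**The model family is not stated.** A binomial or patient-level model fixes the sampling variance, so slope variance can be estimated across 134 facilities. This also stands; the non-identifiability belongs to a Gaussian model with a free residual. In the patient-level case the intercept-and-slope option already contains the facility-by-year effect, and the only weakness is that the plan allows it to be dropped.

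**Slopes are only to be considered, and a fallback is written in.** A reader might infer that the whole disparity result depends on inestimable slopes. The text does not support that. A separate patient-level logistic model with an intervention-by-race interaction, adjusted for clustering, also addresses disparity.

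**The efficiency loss makes nothing wrong.** The change score is valid, the outcome is secondary, and power is claimed for the primary aim only. At ICC 0.05 and 4.8 points the gap is modest. All of this stands.

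**ANCOVA alone would lose question (i).** It does not estimate change within each arm. This stands and shapes the fix.

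The number of occasions and the model family could reasonably be left to a fuller document. The selection rule is different, because the article does state it.

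**Conclusion.** The point holds as an improvement available at no cost. It does not correct an invalid analysis. Given two annual facility proportions in a Gaussian model, the selection rule cannot be applied, and the fallback has 1.62 times (ICC 0.01) or 1.24 times (ICC 0.05) the variance of a baseline-adjusted analysis, with 30 African American patients per facility and fully persistent facility effects. Over the assumed correlations of 0.12 to 0.71 the ratio runs from about 1.8 down to 1.2.

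Two stronger readings should be avoided. One is that a stated power figure is wrong: the article's figure concerns the primary outcome and reproduces. The other is that the plan has a type I error of 7 to 11%. That range applies only if the model is fitted to patient-level data and the slope is dropped although facility effects differ between years, at the upper ICC and an assumed between-year correlation of 0.7 to 0.9. How often the rule would wrongly drop the slope has not been worked out.

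**What to change.** State how many occasions per facility enter the mixed model, and remove the trajectory-based choice of random effects.

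- **Two annual values.** Fit the mixed model with time and time by arm but no arm main effect at month 0, so that the baseline means are equal across arms, as randomisation implies. The arm contrast is then the follow-up difference minus rho times the baseline difference, with variance proportional to 1 − rho², as for ANCOVA. The model still estimates change within each arm, so question (i) is kept, and it brings the secondary analysis into line with the baseline adjustment of the primary one. ANCOVA on the 2014 value may serve for the between-arm test only.
- **Patient-level or monthly data.** Say so, and keep the facility-by-time random effect whatever the plots show. Monthly plots would not rescue the rule: 30 × 0.14/12 = 0.35 referrals per facility-month leaves about exp(−0.35) = 70% of facility-months at zero.

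The cost is a few sentences and model code. No new data are needed.

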To examine the absolute increase of the intervention on AA ESRD patient referrals, patient-level logistic regression analysis will be performed with intervention status, race (AA versus whites) as primary independent variables and controlling for patient-level baseline characteristics. Because patients are clustered within facilities, we will adjust for the clustering effect. Interactions between intervention and race will be included to test for the differential intervention effects by race. For interpretation of findings, we will compare and contrast the standardized predicted referral rates by racial group within the intervention and control facilities, respectively.

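### The patient-level logistic model does not list the facility's 2013 referral rate, a covariate the trial already holds; adding it is a free precision gain, small at ICC 0.01 and possibly material at ICC 0.05.

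*Protocol article*

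**What the plan says.** The Statistical analyses section describes three modelled analyses.

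- **Primary outcome.** ANCOVA on facility referral rates, "after adjusting for the baseline referral rates and facility characteristics that differed significantly across the two arms at baseline".
- **Secondary outcome.** A mixed effects model for the proportion of AA patients referred, with time (baseline as month 0), arm, their interaction, and facility random intercepts, with random slopes if needed.
- **Absolute effect on AA referrals.** Here "patient-level logistic regression analysis will be performed with intervention status, race (AA versus whites) as primary independent variables and controlling for patient-level baseline characteristics". The article adds: "Because patients are clustered within facilities, we will adjust for the clustering effect" and "Interactions between intervention and race will be included to test for the differential intervention effects by race". Results are to be read through standardized predicted referral rates by race and arm.

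No facility-level covariate is named for the third model. The 2013 rate is nevertheless available, because Outcome measures defines it for the primary outcome: "Baseline referral will be calculated as the average number of unique referrals in a dialysis facility over the 12-month period preceding the intervention", that is, January to December 2013. The Power and sample size section allows for facility differences through an "intra-cluster correlation coefficient (ICC) of 0.01 to 0.05".

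**The concern.** Of the three models, the patient-level one is the only one whose description makes no use of the 2013 data. Adjusting for clustering makes the standard error honest about differences between facilities. It does not explain any of those differences, so it recovers no precision. A facility's own rate in the preceding year is an obvious predictor of its rate in the trial year, and it costs nothing to include.

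Two things are at stake.

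- **Precision.** The intervention effect in this model has a larger variance than the data require.
- **Chance imbalance.** The article describes allocation by random number across 134 facilities and mentions no stratification. The arms may therefore differ somewhat in baseline referral. The section's general rule adjusts only for baseline differences that are statistically significant, and the article does not say whether that rule reaches this model. A prognostic but non-significant difference would stay in the estimate, whereas the ANCOVA adjusts for baseline referral in any case.

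**Working it through.** **Inputs from the protocol article.** 67 facilities per arm, m = 46 patients per facility, control referral 14%, 5% significance level (taken as two-sided), 80% power, ICC 0.01 to 0.05 (all from Power and sample size calculations). AA share of the randomized facilities 65.4% (Table 1), so 46 × 0.654 ≈ 30 AA patients per facility.

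**Assumed input.** c, the correlation between a facility's true 2013 and 2014 rates. The document does not give it, so a range of 0.5 to 1 is used.

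**Step 1: reproduce the stated power.** Effective n per arm = 67 × 46 / [1 + (46 − 1) × ICC].

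- ICC 0.01: 3082 / 1.45 = 2126; detectable difference at 80% power 3.11 points (stated: 3.1).
- ICC 0.05: 3082 / 3.25 = 948; detectable difference 4.76 points (stated: 4.8).

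Both figures reproduce. They concern the primary comparison, but they give a fair scale for this model too.

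**Step 2: variance removed by the 2013 rate.** The correlation between the observed 2013 and 2014 facility rates is r = c × m × ICC / [1 + (m − 1) × ICC]. Adjustment multiplies the variance of the intervention effect by (1 − r²).

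- ICC 0.01, m = 46: reliability 0.46 / 1.45 = 0.317; r² = 0.025 (c = 0.5), 0.064 (0.8), 0.101 (1).
- ICC 0.05, m = 46: reliability 2.30 / 3.25 = 0.708; r² = 0.125, 0.321, 0.501.

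**Step 3: power after adjustment, starting from 80%.** Power = Φ[(1.960 + 0.842) / √(1 − r²) − 1.960]. Example, ICC 0.05 and c = 0.8: 2.802 / √0.679 − 1.960 = 1.44, which gives 92.5%.

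| Patients per facility | ICC | c = 0.5 | c = 0.8 | c = 1 |
|---|---|---|---|---|
| 46 (all) | 0.01 | 81.0% | 82.5% | 84.0% |
| 46 (all) | 0.03 | 83.4% | 88.8% | 93.3% |
| 46 (all) | 0.05 | 85.0% | 92.5% | 97.8% |
| 30 (AA) | 0.01 | 80.5% | 81.4% | 82.1% |
| 30 (AA) | 0.05 | 83.7% | 89.5% | 94.4% |

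The gain is about 1 to 4 points at ICC 0.01 and about 4 to 18 points at ICC 0.05.

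**Step 4: simulation check.** 1000 trials per setting; 30 AA patients per facility in 2014; a logistic model with facility-robust standard errors; the 2013 rate taken from all 46 patients. True differences were 3.66 points (ICC 0.01) and 5.14 points (ICC 0.05), which the formula puts at 80% power without adjustment.

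| ICC | c | Power without 2013 rate | Power with 2013 rate |
|---|---|---|---|
| 0.01 | 0.5 | 79.9% | 80.4% |
| 0.01 | 0.8 | 79.0% | 80.2% |
| 0.01 | 1 | 80.1% | 83.7% |
| 0.05 | 0.5 | 76.9% | 81.1% |
| 0.05 | 0.8 | 75.7% | 88.2% |
| 0.05 | 1 | 74.3% | 94.8% |

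The pattern agrees with the formula. The last row shows a gain of 20.5 points, slightly above the formula's range, because the simulated start was below 80% and the 2013 rate came from all patients rather than AA patients alone. The simulation has no race term, interaction or patient covariates, so it speaks to the intervention effect only.

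**Step 5: size of chance imbalance.** The SD of the between-arm difference in true facility rates is √(ICC × 0.14 × 0.86) × √(2/67).

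- ICC 0.01: 0.0347 × 0.173 = 0.6 points, 19% of the 3.1-point detectable difference.
- ICC 0.05: 0.0776 × 0.173 = 1.3 points, 28% of the 4.8-point detectable difference.

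Imbalance of this order carries into the unadjusted estimate to the extent that facility rates persist from 2013 to 2014.

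**The case against.** The strongest reply is that nothing here is an error. With clustering accounted for, the test is valid, and under randomization the omitted covariate causes no bias. That stands.

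It can also be said that the mixed effects model already analyses AA referral with baseline as month 0 and facility random intercepts, so the trial does have an analysis of AA referral that uses 2013 data. That stands too, and it lowers the stakes. Moreover, the only hypothesis explicitly tied to the logistic model is the intervention-by-race interaction. That is largely a within-facility contrast, which an overall facility rate would sharpen less.

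A further reply is that exact covariate lists belong in the analysis plan, which is not shown. This stands only in part. The article does name the kind of covariate for this model (patient-level) and names baseline referral for the ANCOVA, so a reader following the text would leave the rate out here.

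The rule on significant baseline differences would catch a marked imbalance if it applies to this model. It would not catch a moderate one and does not deliver the precision gain.

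A reader might infer that the model loses much of its power if facilities differ as the power section assumes. The document does not support that. The section assumes a range of ICCs, and at its lower end the loss is at most about 4 points even with perfectly stable facility rates. The larger losses need an ICC near 0.05 together with a year-to-year correlation of about 0.8 or more, which is nowhere documented. That correlation could be lower, because facilities were selected for low referral or a racial disparity and regression to the mean is plausible.

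**Conclusion.** The point holds as a matter of efficiency in a non-primary analysis. As described, the patient-level model leaves out a prognostic covariate that the trial computes for every facility. Starting from 80% power, including it would gain about 1 to 4 points at ICC 0.01 and about 4 to 18 points at ICC 0.05, for an assumed 2013 to 2014 correlation of facility rates between 0.5 and 1. At ICC 0.05 the gain is about 4 to 5 points with a correlation of 0.5, 10 to 13 with 0.8, and 14 to 18 with 1. The race-by-intervention term gains less.

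A reader might also infer that any disagreement between this model and the ANCOVA would come only from baseline adjustment. That does not follow. The two also differ in unit of analysis, weighting, scale, and race and patient covariates. Unadjusted baseline imbalance is one possible source of divergence among several.

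**What to change.** Prespecify the facility's 2013 referral rate among patients under 70 as a fixed covariate in the patient-level logistic model, regardless of any baseline significance test. It can be the overall or a race-specific rate, suitably smoothed (for example a smoothed logit) so that facilities with few or no 2013 referrals are handled stably. Keep the clustering adjustment, the interaction and the standardized predicted referral rates. Reporting on the standardized scale also means that the added covariate does not change the meaning of the reported quantity, as it would for a conditional odds ratio.

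The cost is one sentence in the plan and one extra model term. The overall rate is already computed for the primary analysis, and race-specific baseline proportions are needed for the secondary outcome anyway.

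### Disparity reduction is defined as an AA-white difference in proportions, but no stated test clearly targets that contrast

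*Protocol article*

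**What the plan says.** All references are to the protocol article.

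- **Definition.** Outcome measures fixes the scale: "The reduction in racial disparity will be measured as the difference in the proportion of referrals among AA vs. whites". The facility selection rule under Target population also uses a difference between the AA and white proportions referred.
- **Model named for this outcome.** Statistical analyses introduces a facility-level analysis for the secondary outcome: "A mixed effects model will be used to test for differences in the proportion of AA patients referred between baseline and 12-month follow up". The next sentence lists time, intervention status and "their interaction on referral disparity, averaged across different subpopulation of facilities will be assessed". Disparity is not defined there as a dependent variable, and white patients have no stated place in the model.
- **Patient-level model.** The same section adds a further analysis whose purpose is stated as "To examine the absolute increase of the intervention on AA ESRD patient referrals". It says "patient-level logistic regression analysis will be performed with intervention status, race (AA versus whites) as primary independent variables", with adjustment for clustering. Then: "Interactions between intervention and race will be included to test for the differential intervention effects by race".
- **Probability-scale output.** The paragraph ends: "For interpretation of findings, we will compare and contrast the standardized predicted referral rates by racial group within the intervention and control facilities, respectively". No test or interval is named for any contrast of these rates.

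**The concern.** The protocol chose an additive definition of disparity, so the inference about disparity should be additive as well. Neither described test clearly is.

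If the mixed model concerns AA patients only, its time-by-intervention term shows whether AA referral rose more in intervention facilities. It does not show whether the gap to white patients narrowed, because white referral may have risen by as much or more.

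The logistic interaction does bring race in, but on the log-odds scale. When two groups start from different proportions, equal odds ratios do not mean equal absolute changes. The conditions for divergence are plausible here: 75 of the 134 facilities were chosen for a racial disparity in referral, and the intervention is meant to raise referral.

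The practical risk is that a null interaction is reported as no change in disparity although disparity, as the protocol defines it, has widened.

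**Working it through.** **Inputs from the protocol article.** 67 facilities per arm with 46 patients each; ICC 0.01 to 0.05; 80% power at 5% significance; detectable difference 3.1% to 4.8% (Power and sample size calculations). "The power calculation assumes a 14% crude referral proportion in the control group", with no split by race. Randomized facilities are 65.4% AA and 33.5% white (Table 1).

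**Assumptions.** The race-specific control rates below are assumed, because the document gives none. Tests are taken as two-sided.

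**Step 1: the plan's own figure.** Patients per arm: 67 × 46 = 3,082. Design effect: 1 + 45 × ICC. Power = Φ(d / √[(0.14 × 0.86 + p₂(1 − p₂)) / n_eff] − 1.96), with p₂ = 0.14 + d.

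- ICC 0.01: design effect 1.45, n_eff = 2,126. At d = 0.031 the standard error is 0.0111 and power is 79.7%.
- ICC 0.05: design effect 3.25, n_eff = 948. At d = 0.048 the standard error is 0.0170 and power is 80.8% (80.6% with a pooled null variance).

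The 3.1 to 4.8 points reproduce and serve below as the planned size of effect.

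**Step 2: null odds-scale interaction.** Apply one odds ratio to both races.

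- 12% AA, 16% white, OR 1.5. AA odds: 0.12/0.88 × 1.5 = 0.2045, so 17.0%. White odds: 0.16/0.84 × 1.5 = 0.2857, so 22.2%. The interaction is exactly 1.00 and the gap goes from 4.0 to 5.2 points. The AA proportion alone rises by 5.0 points, so an AA-only model would look favourable. With weights 65.4/98.9 and 33.5/98.9 the overall rise is 0.661 × 5.0 + 0.339 × 6.2 = 5.4 points, slightly above the planned range.
- 5% AA, 8% white, OR 2.0: 9.5% and 14.8%; the gap goes from 3.0 to 5.3 points.

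Holding the overall rise at 4.8 points and solving for the common odds ratio gives the table below. The last column is the ratio of odds ratios (ROR) favouring AA at which the gap would stay unchanged, with the white rate held at its common-OR value.

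| Control AA / white | Common OR | Intervention AA / white | Gap (points) | ROR for unchanged gap |
|---|---|---|---|---|
| 13% / 14% | 1.44 | 17.7% / 19.0% | 1.0 to 1.3 | 1.02 |
| 13% / 16% | 1.42 | 17.5% / 21.3% | 3.0 to 3.8 | 1.055 |
| 12% / 18% | 1.43 | 16.3% / 23.8% | 6.0 to 7.6 | 1.12 |
| 10% / 20% | 1.45 | 13.9% / 26.6% | 10.0 to 12.7 | 1.24 |
| 5% / 8% | 1.90 | 9.1% / 14.2% | 3.0 to 5.1 | 1.26 |

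**Step 3: point estimate favouring AA patients.**

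- AA 12% to 16.2% (OR 1.42) and white 18% to 23% (OR 1.36) give ROR 1.04 in favour of AA patients, while the gap grows from 6.0 to 6.8 points.
- A rise of 5 points in both races (12 to 17, 16 to 21) leaves the gap at 4.0. The odds ratios are 1.502 and 1.396, so ROR is 1.08 although nothing has changed on the defined scale.

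**Step 4: could such a reversal be significant?** Each arm has about 2,038 AA and 1,044 white patients. The smallest significant ROR is exp(1.96 × √Σ 1/[n p(1 − p)]) over the four cells, ignoring clustering. For 12/18% rising to 16.3/23.8%: Σ = 0.00465 + 0.00360 + 0.00649 + 0.00528 = 0.0200, its root is 0.1415, and the threshold is 1.32. At a 4.8-point rise the gap stops widening at ROR 1.02 to 1.26, below that threshold. Of the cases examined, only 10/20% with an assumed 10-point rise crossed it (gap unchanged at 1.37, threshold 1.31).

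**The case against.** The strongest reply is that the protocol does not make the logistic interaction its disparity test. It names a mixed model for the secondary outcome. The logistic paragraph serves a neighbouring objective, the absolute increase in AA referrals, which Outcome measures lists separately. It also promises standardized predicted rates by race and arm, in which any widening of the gap would be visible. The interval method for those rates is detail that an article may leave to the analysis plan.

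Much of this stands. A reader might infer that the p-value for disparity reduction comes from the odds-scale interaction; the document does not say so. The magnitudes rest on assumed race-specific rates, and the direction requires AA referral to start below white referral. That was the selection criterion for 75 facilities, while the other 59 were selected on low overall referral.

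The reply does not supply the missing test. The mixed model is described by its AA proportion, with disparity named once and left undefined, so it is not clear that an AA-white difference is modelled at all. The predicted rates are on the right scale but are offered for interpretation only. The gap is not only a missing interval formula: the article never says which contrast carries the inference about disparity.

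**Conclusion.** The point holds in limited form. Disparity reduction is defined as a difference in proportions, and no stated test clearly addresses that difference: one model may be AA-only and the other tests race on the odds scale. Under the assumed starting rates and a 4.8-point overall rise, a null interaction goes with a gap wider by about 0.3 to 2.7 points. At 12/18%, any ROR from 1.00 to about 1.12 favours AA patients while the gap widens.

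A reader might go further and expect a significant odds-scale benefit alongside a worsening disparity. The figures do not support that at the planned effect size, since significance needs an ROR of about 1.32. The realistic failure is a null or mildly favourable interaction read as a statement about the defined gap.

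An additive test would not make such small changes easy to detect. At 12/18% the widening of 1.6 points has a standard error of about 2.1 points, ignoring clustering. What it gives is an estimate and interval that answer the stated question. Because this is the declared secondary outcome and the remedy is nearly free, the change should be made.

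**What to change.** 1. Name one disparity contrast on the proportion scale: (AA minus white) in intervention facilities minus (AA minus white) in control facilities.
2. Estimate and test it from the standardized predicted referral rates already planned, with a delta-method or bootstrap confidence interval that respects clustering by facility.
3. Keep the intervention-by-race interaction on the odds scale as supportive, labelled as a ratio of odds ratios.
4. State the mixed model's dependent variable. Either make it the facility's AA-white difference in proportions, or say that the model concerns AA patients only and does not test disparity.

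The cost is a few lines of post-estimation code and a few sentences of wording. No new data or change to the design is needed.
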